### Evaluating the implementation of the AICP

2.9

#### REACH

2.9.1

Absolute number and percentage of episodes of patients between 2 and 14 years presenting with an acute asthma episode during the study field period seen by any participating paediatric healthcare professionals exposed to the clinical practice established by the AICP for the management of AAs 12 and 24 months after its implementation, and their representativeness (characteristics of the participants compared to those of the target population). We consider that an episode has been exposed to the AICP if the patient has at least one of the recommended practices in an asthma episode registered: (a) assessment and recording of the Pulmonary Score; (b) assessment and recording of asthma symptoms using the PACT, (c) administration of background treatment in cases of persistent asthma symptoms, and/or (d) administration of bronchodilators using an MDI with a spacer chamber in children diagnosed with a mild-to-moderate asthma attack.

#### ADOPTION

2.9.2

Absolute number and percentage of paediatric healthcare professionals adopting the AICP for the management of AAs 12 and 24 months after implementation, and their representativeness (characteristics of professionals/centres adopting the intervention/programme compared to those of professionals/centres potentially eligible to participate in the intervention/programme) (characteristics of adopters/non-adopters). We consider that a professional has adopted the pathway if he/she has registered at least one of the recommended practices in an asthma episode (assessment and recording of the Pulmonary Score; assessment and recording of asthma symptoms using the PACT; administration of background treatment in cases of persistent asthma symptoms; and/or administration of bronchodilators using an MDI with a spacer chamber in children diagnosed with a mild-to-moderate asthma attack) in at least 50% of the episodes attended. This adoption threshold, as a desirable goal for improvement, was proposed by the clinical committee within the research team and agreed with a representation of professionals from different levels of care after having considered baseline levels.

#### IMPLEMENTATION

2.9.3

The degree of fidelity with which the professionals/centres have implemented the AICP and its components for the management of AAs compared to what was planned will be evaluated. For this purpose, a complete record and subsequent description will be made of the implementation process, and any adaptations made to the AICP or its components. In addition, the fidelity of the implementation strategies designed to facilitate the adoption of the AICP by professionals/centres will be evaluated. To this end, we will provide a complete record and subsequent description of each strategy's execution process and documentation of adaptations made. Further, to assess dose, quality of delivery, professionals’ responsiveness, and programme differentiation (33), the exposure of professionals/centres/centres to the strategies will be measured by a questionnaire developed ad-hoc for this project.

In addition, a representative sample of professionals from the different levels of care involved (PC, PEDs, hospital wards, PICU, and paediatric pulmonology department) with high and low adoption and implementation rates of the good practice criteria established by the AICP (administration of bronchodilator with a spacer chamber; assessment and recording of the Pulmonary Score; and assessment and recording of persistent symptoms - asthma severity) will participate in a structured process using a qualitative methodology (discussion groups) focused on identifying the main barriers and facilitators for the provision of recommended clinical practice. A purposive sample of paediatricians will be recruited stratified by level of care seeking to ensure that all views are represented. All discussion groups will count with at least 6 professionals organized by level of care. Since one of the objectives is for the professionals to express their group perception of the implementation of the AICP at their level of care, we seek to achieve intra-group homogeneity and therefore the possibility of mixing people from different levels of care in the same group is not contemplated. Sampling will continue until saturation is reached, defined as two consecutive discussion groups in which no new additional information is gathered.

The groups will be led by two researchers with experience in qualitative research, as well as knowledge of the clinical field and the project. The discussion groups will be recorded, with prior consent, and transcribed verbatim. The discussion group scripts will explore in detail the determinants of prescribing practice, with questions formulated to explore each of the 14 domains of the Theoretical Domains Framework (TDF) (34, 35). The script will be developed by researchers with expertise in behaviour change and implementation research. The discussion group script and operational procedure will be piloted and refined before the fieldwork. The transcribed texts will be independently reviewed and analysed by two researchers using qualitative techniques derived from discourse analysis with a deductive perspective. The script will be developed by researchers with expertise in behaviour change and implementation research. The discussion group script and the operational procedure will be piloted and refined before the fieldwork. The transcripts will be independently reviewed and analysed by two researchers using qualitative techniques derived from discourse analysis with a deductive perspective. They will used NVivo 15.0 software (QSR International) to manage the data and facilitate analysis. The data will be analysed using an iterative process in which two researchers will independently review the group transcripts and coding using thematic content analysis related to the factors included in the TDF. First, the thematic categories will be identified using the coding guide related to TDF dimensions developed for the study (see Supplementary File S4). Second, the relevance of each TDF construct in the discourse of the discussion group of professionals from each healthcare field will be analysed. Specifically, a score (ranging from −2 to +2) will be assigned to each construct to highlight its importance in the professionals’ discourse (whether it is a topic that appears or does not appear) and the meaning of the association (i.e., whether it is mentioned in positive terms or as a facilitator, or in negative terms as a barrier).

Themes emerging outside the TDF domains will be object of an inductive analysis based on grounded theory (36). To do so, first, recurring words, concepts and themes emerging from participants’ discourse, will be identified and coded within the data. Next, similar codes will be grouped together to form broader themes or categories. Finally, the identified themes will be interpreted, and potential relationships between them will be explored to develop a deeper understanding of the phenomenon under study and to favour the development of a theory on the functioning of the implementation strategy. Any discrepancies in coding or scoring among researchers thorough the present qualitative analysis will be discussed until final consensus is reached.

Furthermore, discussion groups will be organized to explore the perception and experience of the exposed users (family members) regarding the quality of care received for the management of AAs and the response to their concerns and needs. The procedure will be similar to that used with professionals. The sample will include at least 20 relatives or legal guardians of patients treated for episodes of mild-to-moderate AAs at the 5 levels of care involved (at least 4 per level). Specifically, two or three discussion groups will be held with at least eight participants in each. In order to gather insights into the experiences and perspectives of several demographic characteristics, factors such as age, gender or socioeconomic status will be considered during recruitment. Moreover, to assure experiential diversity, at least half of the participants will be relatives of patients who have received care in accordance with AICP, and the other half, relatives of patients in whom such recommended practice did not take place. In this way, within each group, heterogeneity among patients will be examined seeking to better understand their satisfaction and experience with the clinical performance and identify the factors felt to be important by users.

Finally, qualitative analyses will be shared with all participants in order to ensure and validate that they accurately reflect their experiences and perspectives.

#### Maintenance

2.9.4

The sustainability of the AICP implementation will be assessed 36 months after its initial implementation. This will include a complete record and subsequent description of the implementation process (indicators of Reach, Adoption, Implementation), whether the AICP continues to be implemented (institutionalized or not), the resources required for its maintenance, and any adaptations made to the pathway or the implementation strategies. In addition, the change in primary and secondary effectiveness variables will be measured as an indicator of improvement in the management of AAs from 24 to 36 months after the start of the AICP implementation (long-term effectiveness).

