### Implementation objectives

1.2

(a). To assess the reach of the AICP among the population eligible to receive it 12 months after its implementation; determine the extent to which the exposed population is representative of the target population; and ascertain the perception and experience of exposed users (family members) regarding the quality of care received for the management of AAs and the response to their concerns and needs (REACH)(b). To assess the degree of adoption of the AICP by professionals/centres 12 months after its implementation; and determine the degree of representativeness of adopting professionals/centres and the main barriers or difficulties for adoption (ADOPTION)(c). To assess the degree of implementation of the AICP components, their fidelity to the protocols, and any adaptations made; describe the set of actions or strategies necessary for its adequate implementation and the level of exposure of the implementing agents to them; and assess the feasibility and acceptability perceived by professionals regarding the implementation of the pathway, with special emphasis on the identification of barriers, facilitators, and strategies needed to inform future system-wide scaling up (IMPLEMENTATION)(d). To assess the sustainability of AICP implementation in the long term (24 months), resources, and adaptations required (MAINTENANCE).

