### Design and timeline of the study

2.1

A cluster quasi-experimental implementation trial with matched control group evaluated with mixed methods will be conducted in paediatric services of Basque Health Service, Osakidetza. The present study do not imply prospective recruitment of patients as it consists in a study performed under real world circumstances of clinical practice regarding acute asthma management by professionals of participating paediatric services. A two 12-month implementation periods will take place between May 2023 and May 2025, during which components of the implementation strategy to favour adoption of the AICP will be cumulatively deployed. This will involve, first, a set of strategies facilitating initial uptake (from 7 May 2023 to 7 May 2024); and second, a set of strategies related to broad dissemination and communication among professionals and healthcare centres involved (from 7 May 2024 to 7 May 2025) (see Supplementary File S1 for more detailed specification). The quantitative evaluation to assess the results of the implementation of the AICP at professional and patient levels will be carried out considering the year prior to the first implementation period as the baseline measurement, and three post-intervention measurements at 12, 24 and 36 months from initial implementation of the pathway until May 2026. A flow diagram with further description of the study phases is presented in Figure 1. Final quantitative results of study are expected in June 2026. The qualitative evaluation will be carried out upon the completion of the second implementation period through a structured process with discussion groups. These groups will be focused, on the one hand, on the identification of the main barriers and facilitators for the provision of recommended clinical practice by the healthcare professionals, and on the other, on patients’ (and their relatives’) experience and satisfaction with the clinical care received.

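### Sustainability is set at 24 months in the objectives and at 36 months in the methods, and the 24-to-36-month change labelled long-term effectiveness cannot on its own tell a kept gain from no gain

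*Protocol article*

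**What the plan says.** Three parts of the protocol article bear on this point.

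- **Objective 1.2(d), Implementation objectives:** "To assess the sustainability of AICP implementation in the long term (24 months), resources, and adaptations required".
- **Section 2.9.4, Maintenance:** "The sustainability of the AICP implementation will be assessed 36 months after its initial implementation". The section lists the Reach, Adoption and Implementation indicators, whether the pathway is still in use, resources, and adaptations. It then adds change in the primary and secondary "effectiveness variables will be measured as an indicator of improvement in the management of AAs from 24 to 36 months", counted from the start of implementation and labelled long-term effectiveness.
- **Section 2.1, Design and timeline:** over two 12-month periods, "components of the implementation strategy to favour adoption of the AICP will be cumulatively deployed". The first runs from 7 May 2023 to 7 May 2024 and the second from 7 May 2024 to 7 May 2025. There are "three post-intervention measurements at 12, 24 and 36 months from initial implementation of the pathway until May 2026".

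Section 2.8 defines the main and secondary effectiveness outcomes as change from baseline to 12 and 24 months. If the intervention-by-time interaction is significant, it then compares change from baseline to each follow-up point with the control group. Section 2.11 compares the groups over all three follow-ups with adjustment for baseline.

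**The concern.** There are two linked problems.

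The first is a plain contradiction about when sustainability is judged. At month 24 the second wave of strategies is only just ending. Month 24 is also a main effectiveness time point (2.8) and a Reach and Adoption time point (2.9.1, 2.9.2). A sustainability result taken there would restate those results and say nothing about what happens after support stops.

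The second is the effectiveness measure attached to Maintenance. Sustainability asks whether the gain over baseline is still there. Section 2.9.4 asks whether care improved further between months 24 and 36. A pathway that keeps its whole gain shows no improvement on that measure, and so does one that never had an effect. Nor does 2.9.4 say that the change is compared with the control group, although section 2.4 introduces matched controls partly to deal with secular trends.

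The results are meant to inform scaling up across the regional service (section 3). A sustained pathway reported as showing no improvement, or a shared time trend reported as improvement, would mislead that decision.

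**Working it through.** **Step 1. Dates (section 2.1).** The start is 7 May 2023.

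- Start + 24 months = 7 May 2025, the last day of the second implementation period. Follow-up after deployment: 24 − 24 = 0 months.
- Start + 36 months = 7 May 2026. Follow-up after deployment: 36 − 24 = 12 months.

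**Step 2. What the 24-to-36 change identifies.** Let I and C be the intervention and control rates, and let D(t) be the between-group difference in change from baseline:

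D(t) = [I(t) − I(0)] − [C(t) − C(0)]

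The between-group change from 24 to 36 months is D(36) − D(24), so D(36) = D(24) + (24-to-36 change). The change alone does not fix D(36); together with D(24) it does. The same identity holds on the log-odds scale of the planned logistic models.

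Illustration: the 10% and 15% are borrowed from the power statement in 2.11. The month-36 rates are assumed, and controls are held flat at 10%.

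| Scenario | Baseline | Month 24 | Month 36 | D(24) | 24-to-36 change | D(36) |
|---|---|---|---|---|---|---|
| Gain fully kept | 10% | 15% | 15% | +5 | 0 | +5 |
| Partial loss | 10% | 15% | 13% | +5 | −2 | +3 |
| Full loss | 10% | 15% | 10% | +5 | −5 | 0 |
| Further gain | 10% | 15% | 17% | +5 | +2 | +7 |
| Never worked | 10% | 10% | 10% | 0 | 0 | 0 |

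The first and last rows share a 24-to-36 change of 0 but differ by 5 points in D(36). A pathway keeping 3 of its 5 points scores −2, below one that never worked. Adding the D(24) column separates all five rows.

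**Step 3. Why the control group has to be named.** Suppose both groups rise by 2 points between months 24 and 36 (assumed): intervention 15% to 17%, control 10% to 12%. The change within the intervention group is +2, which would read as improvement. The between-group change is (17 − 15) − (12 − 10) = 0.

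**Step 4. Rough precision.** Take the 1,100 primary-care episodes per year from 2.11. Assume 2,200 control episodes (2:1 matching of professionals with equal caseloads), rates of 15% and 10%, independent years, and 20 episodes per professional. The protocol gives no ICC, so a range is shown.

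- Variance of the between-group 24-to-36 change = 2(0.15)(0.85)/1,100 + 2(0.10)(0.90)/2,200 = 0.000232 + 0.000082 = 0.000314.
- 95% half-width at ICC 0: 1.96 × √0.000314 = 3.5 points.
- At ICC 0.05 the design effect is 1 + 19 × 0.05 = 1.95, and the half-width is 3.5 × √1.95 ≈ 4.9 points.

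Under these assumptions a 2-point loss could not be told from no change, so the interval has to be reported and a non-significant change must not be read as maintenance.

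**Step 5. Where D(36) already exists.** Section 2.11 has intervention, time and their interaction as fixed effects over the three follow-ups, which 2.1 dates at 12, 24 and 36 months. D(36) can therefore be estimated from the planned models. Section 2.9.4 does not point to it, and the outcome definitions in 2.8 stop at 24 months.

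**The case against.** A reader might infer that the plan cannot show whether the effect was maintained, or that the Maintenance objective would go unanswered. The document does not support that.

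- The 24-to-36 change is signed, so it shows loss as well as gain. Read with the baseline-to-24-month effect it separates kept, lost and extended effects, as the table shows.
- The abstract announces effectiveness at 12, 24 and 36 months, 2.8 provides comparisons with control at each follow-up point, and 2.11 models all three. The month-36 comparison is already planned.
- The effectiveness change is an addition in 2.9.4. The Reach, Adoption, Implementation, institutionalisation, resource and adaptation items address objective 1.2(d) directly and are untouched by this point.

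Two gentler readings are possible. The 24 months in 1.2(d) might count from the end of the first implementation period, which would give 12 + 24 = 36 months. The document does not say so, and 2.1 counts from initial implementation. The wording in 2.9.4 might also mean change from baseline, measured during the third year. That reading cannot be excluded, but the sentence does not mention baseline. If either was intended, a stated origin and a stated contrast are still needed.

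It is also fair to say that the data run to May 2026 either way and that correcting 1.2(d) means changing one figure. That limits the cost of the fix, but 2.9.4 remains the only section that defines Maintenance, and it does not use the baseline-to-36-month contrast.

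**Conclusion.** The point holds in limited form. The 24-versus-36-month contradiction is plain in the current text, and a 24-month sustainability assessment would have 0 months of follow-up after deployment, against 12 months at month 36. The effectiveness measure in 2.9.4 is framed as improvement and does not name the control group. Alone, it gives the same value for a 5-point gain fully kept and for no gain at all. It is insufficient and mislabelled, but still informative about decay when read with the 24-month effect.

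The dates follow directly from 2.1. The 5-point contrast rests on assumed month-36 rates and flat controls; the identity D(36) = D(24) + change does not. The precision figures depend on the assumed control volume, independent years and ICC range, and serve only to show why intervals are needed. The other Maintenance indicators and the model in 2.11 stand as written.

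**What to change.** 1. In objective 1.2(d), set the sustainability time point to 36 months from initial implementation, matching 2.9.4, and state the origin in both places.
2. In 2.9.4, define long-term effectiveness as the between-group difference in change from baseline to 36 months, with 95% CI, taken from the 2.11 models on their own scale.
3. Beside it, report the between-group change from 24 to 36 months with 95% CI as a measure of decay or further gain, and stop calling it an indicator of improvement.
4. The share of the 24-month effect retained at month 36 is optional. Drop it if the 24-month effect is small or imprecise, because the ratio is then unstable.

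The cost is wording in two sections and one contrast from each planned model (2.11 fits primary care and emergency departments separately). No new data are needed.

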### Data management plan

2.10

This study will be carried out in accordance with international standards for the conduct of epidemiological studies, included in the International Guidelines for Ethical Review of Epidemiological Studies (37). In order to learn about the management of AAs, data will be collected from the health centres and the PED and inpatient care-paediatric pulmonology reference centres of the two HDs. This is a prospective intervention study, where the data will be collected from the EHR, using the data exploitation program of our regional health service (OSABIDE Global). The Primary Care Research Unit of Bizkaia is formally authorized by the Healthcare Directorate of Osakidetza to extract and use data from the EHR for research purposes. A diagnostic search will be carried out for the term asthma with AAs (International Classification of Diseases code J45.901). Data will also be gathered on the number of prescriptions given for inhaled bronchodilators, or inhaled and systemic corticosteroids, the recording of severity using the Pulmonary Score, and the use of a spacer chamber in mild-to-moderate attacks. In the case of prescriptions, only those made using the Basque Health Service prescription platform and associated with AA episodes will be recorded. As this data collection and recording will be performed without naming and without any participation of the patients as it is mainly routine clinical practice data, need for consent was waived by the ethics committee. Conversely, participants in the structured focus group meetings (both professionals and patients’ relatives/caregivers) will be informed about the study and their written informed consent will be obtained concerning the information directly collected from them (see Supplementary Files S5, S6).

All the information regarding the study subjects, either that extracted from EHRs for this research or collected from the participants of focus groups, will be protected and treated confidentially for all purposes, in accordance with the provisions of the Spanish Organic Law 3/2018, of 5 December, on Personal Data Protection and the guarantee of digital rights (LOPD-GDD) and the provisions of Regulation (EU) 2016/679 of the European Parliament and of the Council of 27 April 2016, on the protection of natural persons with regard to the processing of personal data and on the free movement of such data (General Data Protection Regulation). Specifically, all data will be anonymously documented, de-identified, and linked to unique codes that are meaningless outside the context of the system. The resulting database will be exported to a formatted plain text file that will be compressed and encrypted using a secure algorithm, and then, processed and included in a robust and secure database server.

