### Effectiveness objectives

1.1

To evaluate the effectiveness of the implementation of the AICP on: (a) increasing the rate of administration of bronchodilators using a metered-dose inhaler (MDI) with a spacer chamber in children diagnosed with a mild-to-moderate AAs in PC, PEDs, and hospital wards; (b) increasing the Pulmonary Score documentation rate at all levels of care; (c) increasing the rate of recording asthma symptoms using the Pediatric Asthma Control Tool (PACT) (31) in PC and PEDs; and (d) increasing the rate of initiation of background treatment in children with persistent asthma symptoms, in PC and PEDs.

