### Clinical intervention

2.5

The AICP is a structured multidisciplinary care plan that details the essential evidence-based steps in the care of patients with mild-to-moderate AAs and the coordinated practice of the agents involved as dictated by the evidence. In addition, the pathway determines the target population (inclusion/exclusion criteria); the sequence of common best practices during the patient's navigation through the system, according to the best available evidence in terms of: diagnostic methods and criteria, as well as their coding and recording; the provision of care and recommended clinical practices (actions, responsibilities, etc.); the educational activities for the patient and their relatives; the management of the patient and the patient's care; complex situations, management of difficulties and referral criteria; due attention to transitions between care levels and communication between professionals; and the outcomes to be pursued, evaluated and monitored.

In essence, the four core components of evidence-based clinical practice related to acute asthma as stated in the AICP (see Supplementary File S2) are:
•Assessment and recording of the Pulmonary Score;•Assessment and recording of asthma symptoms using the PACT;•Administration of background treatment in cases of persistent asthma symptoms;•Administration of bronchodilators using an MDI with a spacer chamber in children diagnosed with a mild-to-moderate asthma attack.The AICP was built on the model followed in the design of the Integrated Acute Bronchiolitis Care Pathway (29). It was developed based on the consensus of professionals involved in caring for children with asthma at different levels of care and the advice of experts in quality and medical documentation. Work started in 2020 and after an external evaluation process, its first version was approved in April 2021 (under editorial review).

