### Evaluating the effectiveness of the AICP

2.8

The main effectiveness outcome will be the change from baseline to 12 and 24 months in the rates of mild-to-moderate AA episodes seen in PC and the PED in which patients are administered bronchodilators using a MDI with a spacer chamber. We will assess the overall effect of the AICP by testing the interaction between intervention and time of measurement. Should this intervention-by-time interaction be significant (with *p* < 0.05 as the threshold for significance), planned comparisons will be performed to determine whether changes in the AICP group between baseline and each of the follow-up points are significantly different from those observed in the control group. Secondary effectiveness outcomes will be the change from baseline to 12 and 24 months after the implementation of the AICP in: (a) rate of recording of Pulmonary Score at all levels of care; (b) rate of recording of asthma symptoms using the PACT at all levels of care; and lastly, (c) the change in rate of persistent asthma symptoms in children who initiate a background treatment at all levels of care.

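### Recording only attack-linked prescriptions leaves no reliable way to tell a new start of background treatment from a re-prescription at the attack

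*Protocol article*

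**What the plan says.** All references are to the protocol article.

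- **Section 1.1, objective (d):** "increasing the rate of initiation of background treatment in children with persistent asthma symptoms, in PC and PEDs".
- **Section 2.8, secondary outcome (c):** "the change in rate of persistent asthma symptoms in children who initiate a background treatment at all levels of care". This reverses the numerator and denominator of objective (d), which is a separate matter. It too depends on knowing which children initiated treatment.
- **Section 2.10, variables:** "Data will also be gathered on the number of prescriptions given for inhaled bronchodilators, or inhaled and systemic corticosteroids". Attacks are found by a search on a single diagnosis code, J45.901. No start date, new-or-renewal indicator or look-back for earlier treatment is named.
- **Section 2.10, restriction:** for prescriptions, "only those made using the Basque Health Service prescription platform and associated with AA episodes will be recorded". What makes a prescription associated with an episode is not defined.
- **Section 2.10, identifiers:** data are de-identified and "linked to unique codes that are meaningless outside the context of the system".
- **Section 2.5, core component:** "Administration of background treatment in cases of persistent asthma symptoms". Sections 2.9.1 (Reach) and 2.9.2 (Adoption) use the same term, administration, which does not require separating new from continued treatment.

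**The concern.** Initiation is a statement about two times: no background treatment before, and a start now. Section 2.10 keeps only prescriptions tied to the attack, so it describes the second time and discards most of the information on the first. A child treated since a routine visit and re-prescribed at the attack leaves the same trace as a child who starts treatment there.

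The effect is assessed as the intervention-by-time interaction (sections 2.8 and 2.11), so what matters is whether the mixture of starts and re-prescriptions moves in parallel in the two groups. There is reason to doubt it. Under section 2.6 the intervention districts alone receive electronic-record tools that support recording, training, and monthly audit and feedback on the pathway's indicators. These could change how often treatment is re-prescribed at an attack, or how often a prescription is linked to one, without any change in how many untreated children start.

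**Working it through.** **No plan figure to reproduce.** The article gives no rate, effect size or power for this outcome. Its 80% power statement concerns bronchodilators given by inhaler with spacer and plays no part here.

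**What the extraction rule does to each kind of child with persistent symptoms**

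| Child | Recorded under 2.10 | Result for initiation |
|---|---|---|
| Untreated, prescribed at the attack | Yes | Correctly a start |
| Treated since a routine visit, re-prescribed at the attack | Only the re-prescription | Looks like a start |
| Treated since an earlier attack with a linked prescription, re-prescribed now | Both, if the code follows the child and the earlier attack is in the extracted period | Prior use can be seen |
| Treated since a routine visit, not re-prescribed | Nothing | Looks like an untreated child who did not start |
| Untreated, started at a later visit | Depends on the undefined association rule | Undetermined |

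Rows two and four are the problem. The records that would resolve them are excluded at extraction, so an analysis rule written later could not apply to them.

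**Illustration of mechanism only.** Every input below is an assumption; none comes from the documents.

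Let *u* be the share already treated with no visible prior prescription, *w* the share of those re-prescribed at the attack, and *p* the true initiation rate among the untreated.

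Counted rate = *u* × *w* + (1 − *u*) × *p*

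*Equal misclassification.* Take *p* = 0.20 without and 0.30 with the pathway. The true odds ratio is (0.30/0.70)/(0.20/0.80) = 1.71. Use the same *u*, and *w* = 0.50, in both groups:

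- *u* = 0.25: 0.125 + 0.75 × 0.20 = 0.275 against 0.125 + 0.75 × 0.30 = 0.350. Odds ratio 1.42, difference 7.5 points instead of 10.
- *u* = 0.50: 0.25 + 0.50 × 0.20 = 0.350 against 0.25 + 0.50 × 0.30 = 0.400. Odds ratio 1.24, difference 5 points.

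With *w* = 0 the odds ratios are 1.65 (0.150 against 0.225) and 1.59 (0.100 against 0.150). Most of the dilution on the odds scale therefore comes from counting re-prescriptions as starts.

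*Unequal misclassification.* Hold *p* at 0.20 everywhere, so there is no true effect. Let *w* stay at 0.30 in the comparison group and rise from 0.30 to 0.50 in the intervention group. The counted rate in the intervention group then moves as follows, while the comparison group stays at the first value:

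- *u* = 0.20: 0.22 to 0.26
- *u* = 0.40: 0.24 to 0.32
- *u* = 0.60: 0.26 to 0.38

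The false difference in change is *u* × (0.50 − 0.30), or 4, 8 and 12 points. If *w* instead falls from 0.50 to 0.30 in the intervention group and stays at 0.50 in the comparison group, the same formula gives −4, −8 and −12 points. If *w* changes alike in both groups, it gives zero. The sign follows entirely from what is assumed about *w*.

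**The case against.** **An article need not define a new-user rule.** This is fair as far as it goes. Section 2.10 is not a complete variable list: it does not mention the symptom tool (PACT), whose recording is itself a secondary outcome. Had the article merely been silent on prior treatment, there would be no point to make. But the prescription sentence is an explicit exclusion, and followed as written it removes the data such a rule would need.

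**Prior use may be partly visible.** This stands. If the unique code follows a child across episodes, earlier attack-linked prescriptions would show some prior treatment. A reader might infer that starts and renewals cannot be separated at all; that is too strong. What remains hidden is treatment begun at visits not tied to an attack.

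**Later starts.** A reader might also infer that starts made at a review after the attack are lost. The documents do not establish this. They describe no such review, the pathway's attention to transitions between care levels (section 2.5) does not say treatment is begun later in primary care, and a later visit filed under the same episode might be captured. Restricting the outcome to care at the attack is a legitimate scope choice. It also fits the separate models for primary care and emergency departments in section 2.11, whereas a later primary-care start credited to an emergency episode would raise an attribution question.

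**Administration, not initiation.** Under the wording of sections 2.5, 2.9.1 and 2.9.2, prescribing at the attack for an already-treated child satisfies the component and is not an error. This also stands: the mismatch is confined to objective 1.1(d) and outcome 2.8(c), and relabelling would remove it.

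**Conclusion.** The extraction rule in section 2.10 does not support an initiation outcome as sections 1.1(d) and 2.8(c) state it, because a re-prescription at the attack cannot be reliably told from a new start. This rests on reading the restriction literally and on some children already having background treatment begun outside an attack.

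Equal misclassification would mainly dilute the effect. Misclassification that differs between groups could bias it in either direction, and the intervention's recording tools and feedback make a difference plausible. The documents do not allow the size or direction to be estimated. The 4 to 12 points in the illustration should not be read as an expected inflation, since they come wholly from assumed inputs and reverse sign under the opposite assumption. The point concerns one secondary outcome. The primary outcome, and the Reach and Adoption criteria as worded, do not depend on it.

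**What to change.** Choose one of two routes.

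1. **Keep initiation as the outcome.** For background treatment only, widen the extraction in section 2.10 to all prescriptions on the same platform within a fixed look-back before each episode, whatever diagnosis they are linked to. Use the same window in both groups and in all periods; for the baseline year the query must therefore reach back one full window before that year begins. Count initiation only among children with persistent symptoms and no look-back prescription. The documents give no basis for the window's length, so the sponsor should choose and justify it; six months would be one example.
2. **Keep the extraction.** Relabel the outcome in sections 1.1(d) and 2.8(c) as prescription of background treatment at the attack, in line with administration in sections 2.5, 2.9.1 and 2.9.2, and drop the claim to measure new starts.

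Under either route, define what makes a prescription associated with an attack episode (same contact, same coded episode or a time window), and say whether starts at later visits count. If they do not, a look-forward could be a sensitivity analysis.

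Route 1 costs a wider query on a platform already in use and a smaller denominator once already-treated children are removed. It also needs a check that the data authorisation and the consent waiver described in section 2.10 cover prescriptions unrelated to attacks. Route 2 costs only wording, but gives up the question asked in objective 1.1(d).
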